### Outcomes

#### Primary Outcome Measure

The primary outcome is the pneumonia exacerbation rate within 7 days after ciclesonide inhalation. Computed tomography (CT) images taken prior to drug administration and 1 week following treatment will be compared, and efficacy will be confirmed by checking for pneumonia exacerbation. Pneumonia exacerbation will be independently diagnosed by 2 radiologists, who will only refer to the CT images. An exacerbation of pneumonia will be diagnosed if evidence of exacerbation is present on the day 8 CT image compared to the day 1 CT image.

#### Secondary Outcome Measures

Secondary outcome measures include changes in clinical findings, laboratory findings, and the number of quantified SARS-CoV-2 viral genome copies over time. Clinical findings include the following: body temperature, malaise/appetite, oxygen therapy conditions, respiration rate, oxygen saturation, systolic blood pressure, heart rate, level of consciousness, hospital discharge, ventilator use, extracorporeal membrane oxygenation use, presence of intensive care unit management, and miscellaneous combined medicine conditions.

Laboratory findings include the following: albumin level, lymphocyte count, C-reactive protein level, D-dimer level, leukocyte count, hemoglobin level, platelet count, blood sedimentation, bilirubin level, aspartate transaminase level, alanine transaminase level, lactate dehydrogenase level, γ-glutamyl transpeptidase level, alkaline phosphatase level, creatine kinase level, creatinine level, blood urea nitrogen level, sodium level, potassium level, glutamic acid level, and procalcitonin level.

The safety endpoint will be based on adverse event frequency/percentage.

### Participant Timeline

Figure 2 and Table 1 show the schedule of enrollment, interventions, and assessments. Data collection will occur at screening (ie, day 1), day 2 (ie, randomization period), and days 4, 8, 15, 22, and 29. 

**Figure 2 figure2:**
[figure not shown]
Participant timeline, enrollment, interventions, and assessments.

**Table 1 table1:** Assessment details and days of implementation.

Assessment	Screening period	Administration period	Observation period	Suspension
Hematologic test^a^	Day 1	Days 4 and 8	Day 15: implemented as an outpatient examination when the research subject has been discharged. Days 22 and 29: unnecessary when the research subject has been discharged.	Unnecessary when the research subject has been discharged
Biochemical blood inspection^b^	Day 1	Days 4 and 8	Day 15: implemented as an outpatient examination when the research subject has been discharged. Days 22 and 29: unnecessary when the research subject has been discharged.	Unnecessary when the research subject has been discharged
Infectious disease inspection^c^	Day 1	Not implemented	Not implemented	Not implemented
Coagulation test^d^	Day 1	Days 4 and 8	Day 15: implemented as an outpatient examination when the research subject has been discharged. Days 22 and 29: unnecessary when the research subject has been discharged.	Unnecessary when the research subject has been discharged
Coronavirus inspection^e^	Day 1	Day 8	Day 15: implemented as an outpatient examination when the research subject has been discharged.	Implemented when suspended before Day 8
Image inspection^f^	Day 1	Day 8	Day 15 Days 22 and 29: unnecessary when the research subject has been discharged.	Implemented when suspended before Day 8
Peak flow measurement^g^	Day 1	Performed daily	Days 15, 22, and 29	Not implemented
Questionnaire^h^	Day 1	Subjective symptoms recorded daily	Day 15: implemented as an outpatient examination when the research subject has been discharged. Days 22 and 19: obtained by phone when the research subject has been discharged.	Obtained by phone when the research subject has been discharged
Comprehensive assessment by the physician	Day 1	Day 8	Day 15: implemented as an outpatient examination when the research subject has been discharged. Days 22 and 29: unnecessary when the research subject has been discharged.	Unnecessary when the research subject has been discharged
Confirmation of combined drug usage conditions^i^	Not implemented	Information on the presence of concomitant medications collected daily	Days 15, 22, and 29	Not implemented

^a^Leukocyte count, neutrophil count, lymphocyte count, hematocrit level, hemoglobin level, platelet count, and blood sedimentation are to be measured for the hematologic tests.

^b^Albumin, bilirubin, aspartate transaminase, alanine transaminase, lactate dehydrogenase, γ-glutamyl transpeptidase, alkaline phosphatase, creatinine kinase, creatinine, blood urea nitrogen, sodium, potassium, C-reactive protein, glutamic acid, and procalcitonin levels are to be measured for biochemical blood inspections.

^c^Hepatitis B surface antigens, hepatitis B core antibodies, hepatitis C virus antibodies, and HIV antibodies are to be measured for infectious disease inspections.

^d^Prothrombin time, activated partial thromboplastin time, fibrinogen level, and D-dimer level are to be measured for coagulation tests.

^e^For coronavirus inspections, SARS-CoV-2 real-time polymerase chain reaction samples are to be collected with nasal swabs and measured on the day of and 8 days after hospitalization, and serum SARS-CoV-2 antibodies are to be measured on the day of and 8 days after hospitalization.

^f^Chest computed tomography scans are to be taken on the day of and 8 days after hospitalization, and simple chest radiographs are to be taken 4, 8, 15, 22, and 29 days after hospitalization. In addition, image inspections will be conducted as necessary when symptom exacerbation is suspected. Simple chest radiographs on days 22 and 29 will not be taken if the research subject is already discharged. Computed tomography is to be performed when pneumonia worsens within 8 days of hospitalization and when the research is suspended.

^g^Peak expiratory flow is to be measured every morning with a peak flow meter during hospitalization and recorded in a diary.

^h^To be conducted prior to assessment by the physician (eg, before the examination).

^i^Information on drug and treatments other than the trial drug are to be collected.

### Data Collection Items and Management

With regard to research subject demographics and background medical information, the following demographic and medical data will be collected: sex, birth date (ie, age), initials, nationality, ethnicity, height, smoking history (ie, presence/absence, the number of cigarettes per day, and the number of years of smoking), complications, medical history, history of present illness, drug allergies, COVID-19 onset date, PCR positivity date, level of consciousness, hospitalization conditions, ventilator use, extracorporeal membrane oxygenation use, oxygen therapy conditions, physical activity conditions, the presence of intensive care unit management, and miscellaneous combined drug conditions. With regard to subjective and objective symptoms, data on physical findings confirmed through visual, tactile, auditory, and percussion inspections will be collected.

With regard to adverse event observation, in cases where adverse events are confirmed in the research subject, the following information will be confirmed, and the content will be recorded in the clinical record and case report: adverse event name, extent, severity assessment, causal relationship, onset time, outcome, and elimination period.

With regard to vital signs, the following data will be collected during resting conditions: blood pressure, pulse rate, respiratory rate, body temperature, and oxygen saturation. In terms of body weight measurements, body weight and body mass index will be recorded.

Details for blood sample collection are found in Textbox 2.

Blood sample collection and analysis.
**Hematologic test**
The following were measured at each implementing institution: leukocyte count, neutrophil count, lymphocyte count, hematocrit level, hemoglobin level, platelet count, and blood sedimentation.
**Biochemical blood inspection**
The following were measured at each implementing institution: albumin level, bilirubin level, aspartate transaminase level, alanine transaminase level, lactate dehydrogenase level, γ-glutamyl transpeptidase level, alkaline phosphate level, creatinine kinase level, creatine level, blood urea nitrogen level, sodium level, potassium level, C-reactive protein level, glutamic acid level, and procalcitonin level.
**Infectious disease inspection**
The following were measured at each implementing institution: hepatitis B surface antigen level, hepatitis B core antibody level, hepatitis C virus antibody level, and HIV antibody level.
**Coagulation test**
The following were measured at each implementing medical institution: prothrombin time, activated partial thromboplastin time, fibrinogen level, and D-dimer level.
**Coronavirus inspection**
Nasal swabs will be taken to test for SARS-CoV-2 infection via real-time polymerase chain reaction. Samples will be temporarily stored at each participating medical institution (ie, stored at below −80°C for blood serum), collected by the National Center for Global Health and Medicine, and quantified at the Tokyo Metropolitan Institute of Public Health.Serum samples will be taken to test for the presence of SARS-CoV-2 antibodies. Samples will be temporarily stored at each implementing medical institution (ie, stored at below −80°C for blood serum) and quantified at the National Center for Global Health and Medicine.

The following will be performed for image inspection: high-resolution CT on days 1 and 8, and chest radiography on days 1, 8, 15, 22, and 29.

With regard to peak expiratory flow, measurements will be performed every morning with a peak flow meter and recorded in a diary.

A questionnaire assessment using a 10-stage assessment scale for appetite, fatigue, and cough will be issued on days 1-8, 15, 22, and 29. This questionnaire is to be administered prior to the physician-based assessment (eg, diagnosis) to eliminate bias. The subphysician is not to behave in a manner that induces answers from respondents, and the respondent who is handed the questionnaire must respond to it individually.

A comprehensive assessment is to be conducted by the physician. For this assessment, a 3-stage assessment for general patient conditions is to be conducted on days 8 and 15, relative to day 1. The confirmation of combined drug use conditions will begin on the start date of drug administration and continue until the administration period is complete. Trial drug/combined drug administration conditions will also be recorded.

Discharge outcomes are to be recorded.

Data input into the case report and inquiry responses are to be conducted through the EDC system (REDCap [Research Electronic Data Capture]). A manual with details on inputting data, such as input methods and duration, has been created. Chest CT images and simple chest radiographs taken when research is suspended due to pneumonia onset within 7 days of administration will be sent to the Center Hospital of the National Center for Global Health and Medicine by CD-ROM.

### Adverse Event Reporting

The incidence of adverse events, including abnormal variations in clinical inspection values and physiological function inspections, will be recorded. Adverse event incidence duration/elimination duration, extent, treatment, outcomes, severity assessments, correlation with medicinal drugs, and predictability are to be recorded in the diagnostic record and case report.

Adverse event extent will be determined based on certain criteria. Mild adverse events refer to conditions in which continued drug administration is possible with no treatment. Moderate adverse events refer to conditions in which continued drug administration is possible with some form of treatment. Severe adverse events refer to conditions in which drug administration is or should be suspended.

Adverse event severity will be determined using the following criteria: (1) death, (2) conditions that may lead to death, (3) conditions for which hospitalization at a medical institution is necessary or hospitalization duration must be extended for treatment (4) disorders, (5) conditions that may lead to disorders, (6) conditions that are severe according to criteria 1-5, and (7) congenital illnesses or abnormalities due to prior generations. All conditions that are not considered severe will be categorized as nonsevere.

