### Objectives

The primary objective of the RACCO (Randomized Ciclesonide COVID-19) trial is to compare the pneumonia exacerbation rate between the ciclesonide and symptomatic treatment groups, which consist of patients with COVID-19, and to determine the efficacy of ciclesonide. The secondary objective is to investigate the safety of ciclesonide administration by comparing the rate of adverse events between both groups. In addition, changes in clinical and laboratory findings and changes in the number of copies of the viral genome over time will be monitored between the 2 treatment groups.

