### Interventions

Participants will be randomized to 1 of the 2 treatment groups. In the ciclesonide group, a 400-µg dose of ALVESCO, which is manufactured by Teijin Pharma Limited, Japan, will be administered to patients with asymptomatic or mild COVID-19 3 times per day over a continuous 7-day period. The patients will also receive antitussives and antipyretics as needed. In the symptomatic treatment group, only antitussives and antipyretics will be administered to the patients as needed.

Ciclesonide has not been approved for COVID-19 treatment in Japan or internationally, and is used only for research purposes.

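### Adverse event extent is graded only by whether drug administration can continue, so any table of events by extent would not compare the two arms alike; *severe* also carries two meanings

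*Protocol article*

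**What the plan says.** The article sets up two classifications in consecutive paragraphs of Adverse Event Reporting.

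- **Extent**, in three grades. The lowest is worded "Mild adverse events refer to conditions in which continued drug administration is possible with no treatment". The middle grade differs from it only in that the event needs treating while the drug goes on. The top grade is worded "Severe adverse events refer to conditions in which drug administration is or should be suspended".
- **Severity**, in two classes: "Adverse event severity will be determined using the following criteria: (1) death, (2) conditions that may lead to death", followed by hospital admission or a longer stay, disorders, conditions that may lead to disorders, a sixth item worded "6) conditions that are severe according to criteria 1-5", and congenital illness. It closes with "All conditions that are not considered severe will be categorized as nonsevere".

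Extent and severity are listed as separate items to be recorded for each event (Adverse Event Reporting; Data Collection Items and Management).

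On treatment, Interventions gives ciclesonide for 7 days in one arm. For the other it says: "In the symptomatic treatment group, only antitussives and antipyretics will be administered to the patients as needed". Provisions of Posttrial Care adds three weeks of follow-up after the treatment week.

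On the comparison, the secondary objective is to "investigate the safety of ciclesonide administration by comparing the rate of adverse events between both groups". The safety set contains all participants (Analysis Sets). The endpoint and its test concern adverse event incidence and rates (Secondary Outcome Measures; Safety Analysis).

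**The concern.** An intensity grade supports a between-arm comparison only if an assessor can apply it in the same way to the same clinical event in either arm. Here every grade is tied to the drug. In the ciclesonide arm during week 1, the top grade can follow from a decision that the investigator actually takes about the inhaler, in a trial where allocation is known. In the symptomatic arm there is no such decision, and after the first week there is none in either arm. The article gives no wording for those situations.

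The two uses of *severe* add a second problem. A count of severe events could mean events that led, or should have led, to suspension of the drug. It could equally mean events that meet the seriousness-type list. A reader of a safety table could not tell which.

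What is at stake is the interpretability of graded adverse event data, which sites are required to record. No planned hypothesis test is at stake.

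**Working it through.** The article states no figure on this point, so there is none to reproduce. The check is a comparison of definitions, with one piece of arithmetic for scale.

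**Step 1. What each extent grade needs.** Mild: administration can continue, no treatment. Moderate: administration can continue, with treatment. Severe: administration is suspended or ought to be. Each grade contains a statement about drug administration, so without a drug none of the three has a literal meaning, and this includes mild and moderate.

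**Step 2. Which drug.** The text says drug administration, not trial drug. Reading it as the trial drug is an inference, though a strong one, because the abstract and Primary Outcome Measure use the same phrase for study treatment.

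**Step 3. How much planned time has a trial drug.** Inputs: 45 patients per arm (Sample Size), 7 days of ciclesonide (Interventions), 1 + 3 weeks = 28 days of participation (Provisions of Posttrial Care).

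- On trial drug: 45 × 7 = 315 patient-days.
- Total: 90 × 28 = 2,520 patient-days. Share on drug: 315 / 2,520 = 12.5%.
- Off drug: symptomatic arm 45 × 28 = 1,260 (50%), plus ciclesonide arm after day 7, 45 × 21 = 945 (37.5%). Together 2,205 (87.5%).
- Counting to day 29 instead: 90 × 29 = 2,610, and 315 / 2,610 = 12.1% on drug.

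**Step 4. The two meanings of severe, side by side.**

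- A minor local effect for which the inhaler is stopped, meeting none of the listed criteria: extent *severe*, severity *nonsevere*.
- An event in a symptomatic-arm patient that lengthens the hospital stay: severity *severe* under the third criterion, with no stated extent grade.

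Disagreement between two axes is legitimate in itself, since intensity and seriousness are different things. The fault is that both axes use the same word for their upper class. The sixth criterion also uses the word inside its own definition. The following section is headed with serious adverse events but defines disease, predictability and causal relationship, not serious.

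**Step 5. Which planned analyses use the grade.** Objectives, Secondary Outcome Measures and Safety Analysis all refer to overall adverse event frequency, incidence or rate. None states a comparison by extent or a count of severe events. Whether an event occurred does not depend on its grade, so these comparisons stand. The primary endpoint is read from CT images and does not use the grade.

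**The case against.** The strongest reply is that nothing planned depends on the grade. This is right, and it limits the point to graded data. A reader might infer that the secondary safety objective is itself compromised. The documents do not support that, because the objective and the test concern the overall rate.

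Second, the scale can be used off drug. The phrase about conditions in which the drug *should* be suspended allows a judgement on the patient's state without any drug having been stopped, and the line between mild and moderate turns on need for treatment, which can be judged in either arm. This also stands in part: the scale is not impossible to apply. What remains is that such grading is hypothetical in one arm and partly based on actual decisions in the other, with no rule to align them.

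Third, a reader might infer a bias against ciclesonide, with control events falling by default into mild or moderate. That does not follow. The lower grades also refer to continued administration, so there is no default, and the article contains nothing from which a direction or size can be derived.

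Fourth, clinically important events are caught by the seven-item list, most of which does not refer to the drug and can be applied in both arms. This is correct, and it makes that list the better basis for a between-arm summary of important events.

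Fifth, the double use of *severe* is probably a labelling or translation matter across two separately recorded fields. This is likely, and it is why relabelling is enough. As printed, the ambiguity remains.

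**Conclusion.** The point holds in a limited form. The extent scale is a stated rule tied to drug administration. It has no literal referent in the symptomatic arm, or in the ciclesonide arm after day 7. Any tabulation by extent would not be comparable between arms. *Severe* has two meanings in adjacent paragraphs.

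On size: 50% of patients never have a trial drug, and about 87.5% of planned patient-days are off it (87.9% if 29 days are counted). These figures describe exposure time. They should not be read as the share of events misgraded or as a measure of bias, particularly as events need not be spread evenly over the month.

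The conclusion rests on two assumptions. Drug administration means the trial drug. Adverse events are also graded during follow-up, which the article implies through its three-week follow-up but does not spell out. Without the second assumption the problem in the ciclesonide arm after day 7 falls away, but that in the symptomatic arm remains.

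The overall adverse event comparison and the primary analysis are unaffected.

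**What to change.** In Adverse Event Reporting and on the case report form:

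1. Define extent by effect on the patient, or by a standard toxicity grading, in the same words for both arms and for the whole adverse event observation period.
2. Record action taken with the trial drug as a separate item.
3. Relabel the seven-item list serious / not serious, and reword the sixth item so that it does not use the term being defined.

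The change adds no visits or procedures. Its cost is revised wording plus regrading of events already entered. The article appeared on December 31, 2020, after the expected end of follow-up on October 31, 2020, so regrading would probably be retrospective. If it is done by sites that know the allocation, it carries its own risk of bias, so it should be done blind to allocation where possible. If regrading is not feasible, make no comparison of arms by extent, and report overall incidence and serious events only.

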### Serious Adverse Events and Disease Reporting

The following procedures will be undertaken when illnesses occur in the present research. With regard to illnesses, this study will use certain definitions relating to disease.

The term “disease” was defined as an illness, disability, mortality, or infectious disease caused by the implementation of the clinical research, as well as clinical inspection value abnormalities or symptoms. “Disease” was also defined as adverse events that have a causal relationship with the proposed research that cannot be refuted.The term “predictability” refers to diseases with incidence tendencies (eg, research subject drug-based disease incidence, the number of incidents, incidence frequency, and incidence conditions) in the disease report that can be predicted from research proposals or documents, explanations, and attached documents that include a summary of the drug. Incidence tendencies that can be predicted will be indicated as “known,” and those that cannot be predicted will be indicated as “unknown.” As a general principle, drugs that have already been approved for research subjects will use the attached documentation as the decision criteria.The term “causal relationship” refers to diseases that have a causal relationship with the proposed research that cannot be refuted. At the very least, the correlation with the research subject drug will be determined as a logical possibility, using the GCP ordinance as a guide.

During the implementation of the proposed research, adverse events will be reported in accordance with national guidelines.

